#### Qualitative Sample Size

To determine the qualitative sample size, we follow the principle of achieving data saturation, which ensures that reoccurring themes are exhausted [44]. With a study that uses IDIs and shared walks—with a relatively focused research question—saturation should occur at approximately 20 interviews or with 20 participants. Therefore, we aim to conduct 5-10 IDIs with HCWs in each of the intervention and control arms (15-30 in total) and 10-15 IDIs with community members in each of the intervention and control arms (30-45 in total).

### Recruitment and Data Collection

Over the course of the study, we will integrate several rounds of quantitative and qualitative data collection with community members, CHVs, and HCWs. For an overview of all data collection instruments, see Table 1.

**Table 1 table1:** Data collection instruments of a mixed methods cluster randomized controlled trial to assess the effectiveness of leprosy sensitization campaigns in rural Togo. A summary of study instruments, respondents, and procedures. Data collection and intervention implementation will take place between March 2023 and June 2024.

Data collection type and instrument			Population and recruitment												Sample size			Estimated duration (minutes)			Timing of data collection
			Population			Observation unit		Sampling unit		Sampling method		Eligibility									
**Quantitative**																					
	Survey baseline		Community members of all 60 study communities			Individual		Households		Random selection		Adult men and women aged ≥18 years, preferably household head and spouse		1200			20			Before Intervention	
	Survey endline		Community members of all 60 study communities			Individual		Households		Random selection		Adult men and women aged ≥18 years, preferably household head and spouse		1200			30			After Intervention	
	Survey CHV^a^		CHVs of all intervention communities			Individual		Community		Census (intervention arm 1 and 2)		CHV of study community		40			20			After Intervention	

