**Objective:**

The primary objective of this study is to assess the causal effect of common practice community sensitization campaigns on leprosy-related knowledge and stigma at the community level and among community health volunteers. Additionally, we will test the potential of novel educational audio tools in the 15 most prominent local languages to overcome literacy and language barriers and amplify sensitization campaigns.

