### Study Objectives

The main objective of this study is to assess the effectiveness of community-based sensitization campaigns to increase leprosy-related knowledge and reduce stigma. Our results will inform national policy and decision makers, as well as stakeholders delivering health services and sensitization campaigns.

Specific research objectives are to (1) establish the effectiveness of community-level sensitization campaigns and local language audio tools to increase knowledge and decrease stigma related to leprosy among community members; (2) determine the effects of leprosy training for CHVs (knowledge on diagnosis, treatment, and prevention); and (3) elucidate the mechanisms and experiences of sensitization interventions among community members, HCWs, and CHVs.

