### Trial Design

We will use a cRCT using a sequential mixed methods design by collecting and analyzing quantitative and qualitative data. The trial will have 2 intervention arms that are randomly assigned across 60 study communities. Intervention arm 1 will receive the sensitization campaign (common practice by the national NTD program). Intervention arm 2 will receive the sensitization campaign (a common practice by the national NTD program) accompanied by audio tools. Control arm will receive no sensitization campaign exposure before endline data collection.

Communities assigned to the control arm will receive intervention arm 1 after data collection to ensure that all communities will receive common practice sensitization campaigns by the end of the study period.

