While we acknowledge that education alone is never as effective as a combination of strategies for stigma reduction [8,32,33], the interventions in this study are designed to primarily target underlying causes and drivers of stigma by addressing knowledge and beliefs about leprosy at the community level. Additionally, the interventions also engage community members in activities aimed directly at reducing stigma. Through the inclusion of audio tools for information dissemination, we aim to acknowledge potential stigma facilitators, such as low literacy rates, in affected groups [30]. Offering learning content in local languages (rather than French), the audio tools could potentially improve campaign effectiveness by increasing self-efficacy through the ability to participate in the intervention as well as being able to understand the content [24-26]. Additionally, our trainings for CHVs and health facility staff in our intervention arms aim to reduce stigma at the organizational and institutional level (for example, avoiding segregation of patients) [15].

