#### Quantitative Study Component

People aged 18 years and older who are resident of the respective community. All CHVs serving a study community and aged 18 years and older will be eligible to participate in the survey.

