#### Quantitative Survey Participants

At baseline, before intervention implementation, community members were sampled through a random selection of households in all 60 study communities. In each community, 10 households were selected following a random walk procedure adjusted to the local context of widely spread farmsteads [45]. In each selected household, one female and one male household member were interviewed, preferably the household head and respective spouse or husband. For the endline survey, the same individuals will be interviewed. All CHVs will be selected for a quantitative survey during the endline data collection.

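### Table 1 surveys community health volunteers only in the two intervention arms and only after the intervention, contradicting the text; if Table 1 governs, no effect among volunteers can be estimated

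*Protocol article*

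**What the plan says.** All references are to the protocol article.

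**Effect claims.** The Objective paragraph of the abstract says the study will "assess the causal effect of common practice community sensitization campaigns on leprosy-related knowledge and stigma at the community level and among community health volunteers". Under Study Objectives, the second specific objective is to "determine the effects of leprosy training for CHVs (knowledge on diagnosis, treatment, and prevention").

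**Who is trained, and when.** Conceptual Framework places the training in the intervention arms ("our trainings for CHVs and health facility staff in our intervention arms"). Implementation dates it to August and September 2023, with endline planned for November 2023. Under Trial Design, "Control arm will receive no sensitization campaign exposure before endline data collection", and control communities receive the arm 1 campaign after data collection.

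**Who is surveyed, according to Table 1.** There is one quantitative CHV row. Its population is the CHVs of the intervention communities, its sampling entry is "Census (intervention arm 1 and 2"), its sample size is 40 and its timing is after the intervention. The two community-member rows of the same table cover all 60 study communities.

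**Who is surveyed, according to the text.** Eligibility Criteria, Quantitative Study Component: "All CHVs serving a study community and aged 18 years and older will be eligible to participate in the survey". Quantitative Survey Participants: "All CHVs will be selected for a quantitative survey during the endline data collection". Neither sentence is limited to the intervention arms.

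**The concern.** An effect needs a comparator: untrained CHVs at the same time, or the same CHVs before training. Table 1 provides neither, although the objectives speak of effects among CHVs. A single survey of trained CHVs describes how much they know and what attitudes they hold. It cannot show how far the campaign or the training changed either.

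The text sections suggest a wider survey that would supply a randomized comparator, so the article gives two incompatible accounts of who is interviewed. The choice matters because the opportunity closes: once control communities receive their delayed campaign, an unexposed CHV group no longer exists. A later analysis plan cannot recover data that were never collected.

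**Working it through.** **1. Does the sample size fit the narrow or the wide survey?** The article states neither the number of communities per arm nor the number of CHVs per community. Assume equal allocation of the 60 communities (20 per arm) and one CHV per community.
- Arms 1 and 2 only: 2 × 20 × 1 = 40, the Table 1 figure.
- All three arms: 3 × 20 × 1 = 60.

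The figure of 40 therefore agrees with the table's population and sampling entries. The restriction does not look like a slip in one cell.

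**2. Which contrasts exist under each reading?**

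| Contrast among CHVs | Table 1 | All CHVs (text sections) |
|---|---|---|
| Trained vs untrained, at endline | no (0 control CHVs) | yes, randomized |
| Before vs after training | no (no CHV baseline) | no (no CHV baseline) |
| Arm 2 vs arm 1 | yes, but both trained | yes, but both trained |

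The baseline sampled community members from households, and the text places the CHV survey at endline, so no pre-training CHV measurement is described on either reading. Arm 2 differs from arm 1 only by the audio tools, so that contrast measures neither the training nor the campaign. Under Table 1 neither effect is identified, whatever the sample size.

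**3. What would a survey in all arms deliver?** Inputs: 40 trained and 20 untrained CHVs (same assumptions as step 1), 5% significance and 80% power as in Quantitative Sample Size. The article does not state sidedness; two-sided is assumed.

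Minimum detectable difference in SD units = (1.96 + 0.84) × √(1/40 + 1/20) = 2.80 × √0.075 = 2.80 × 0.274 ≈ 0.77 SD. A noncentral-t calculation gives 0.78.

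The article gives no SD for CHVs. Its SD of 30 and its target of 10 percentage points belong to the community-member calculation, so a range is shown:

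| Assumed SD (points) | Detectable difference = 0.767 × SD | Power for 10 points |
|---|---|---|
| 10 | 7.7 | 96% |
| 15 | 11.5 | 68% |
| 20 | 15.3 | 45% |
| 25 | 19.2 | 31% |
| 30 | 23.0 | 23% |

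Adding control CHVs makes the effect estimable. Whether it is estimated precisely depends on an SD that is not given.

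**The case against.** **The text sections may state the true intention.** They refer to all CHVs, and the recruitment sentence follows a description of sampling in all 60 communities. On that reading a randomized endline comparison exists, and randomization makes a CHV baseline unnecessary for identification. This stands, and it is why the consequence is conditional on Table 1. A reader might infer that the CHV effect cannot be estimated on any reading; the documents do not support that. They do, however, leave the contradiction in place, and three Table 1 entries (population, sampling and sample size) agree on the narrow survey.

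**The article never claims a causal effect of training.** Correct. In the abstract, the word causal describes the campaign's effect among CHVs; objective 2 speaks of the effects of training without that word. The two statements should not be merged. But CHVs in both surveyed arms are exposed to both, so under Table 1 neither effect has a comparator.

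**CHVs are peripheral to the trial.** Largely fair. A reader might infer that half of the primary objective fails. CHVs appear in the primary objective only in the abstract; the main objective under Study Objectives does not name them, the knowledge outcome is defined for community members, and the sample size calculation and the 1200 respondents concern community members. What is affected is one stated element of the abstract's objective and one of three specific objectives.

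**Control-arm CHVs are already covered qualitatively.** Interviews with 5 to 10 health care workers and CHVs per arm include the control arm. These purposive interviews can inform perceptions and mechanisms but cannot estimate an effect.

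**The added interviews may not be informative.** At an SD of 30, power for 10 points would be about 23%. This stands, and the protocol should state it.

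**Conclusion.** The article contradicts itself on which CHVs are surveyed. If Table 1 governs, neither the campaign's causal effect among CHVs nor the effect of their training can be estimated, because all 40 respondents are trained and none is measured beforehand. If the text sections govern, a randomized endline comparison with untrained CHVs is possible and the Table 1 row is wrong. One of the two must change.

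This conclusion rests on the wording alone. The precision figures (about 0.77 SD, or about 8 to 23 points for an SD of 10 to 30) depend on equal allocation, one CHV per community, a two-sided test and an assumed SD. The main intention-to-treat comparison among community members is untouched.

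**What to change.** **Preferred change.** Make the Table 1 CHV row a census of CHVs in all 60 study communities, so that it agrees with Eligibility Criteria and Quantitative Survey Participants. Specify that control-arm CHVs are interviewed at endline, before their community receives the delayed campaign. Define the CHV effect as arms 1 and 2 combined versus control, with robust standard errors, clustered by community only if some communities have more than one CHV. With one per community, clustering changes little. Report the detectable difference, with its SD assumption, and say that precision is limited.

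**Cost.** About 20 more interviews at Table 1's estimated 20 minutes each (20 × 20 = 400 minutes of interview time), in communities that endline teams visit anyway, plus a short protocol clarification.

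**Fallback.** If control CHVs will not be surveyed, or can no longer be reached before their delayed campaign, remove the CHV effect claims from the abstract's objective and from specific objective 2. Describe the CHV survey as descriptive, and limit the two sentences about all CHVs to the intervention arms. This costs wording only.

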**Qualitative**																					
		In-depth interview cover sheet		HCWs^b^, CHVs and community	Individual		Community		Purposive		Adult men and women aged ≥18 years and HCW, CHV or community member in the respective communities that provide written informed consent		45-75			N/A^c^			During intervention		
		In-depth interview guide		HCWs and CHVs	Individual		Community		Purposive		Adult men and women aged ≥18 years and HCW, CHV or community member in the respective communities that provide written informed consent		15-30			45-60			During intervention		
		Shared walk guide		HCWs and CHVs	Individual		Community		Purposive		Adult men and women aged ≥18 years and HCW, CHV or community member in the respective communities that provide written informed consent		15-20			N/A			During intervention		
		In-depth interview guide		Community members	Individual		Community		Purposive		Adult men and women aged ≥18 years that identify as a community member in the respective communities and provide written informed consent		30-45			45-60			During intervention		

^a^CHV: community health volunteer.

^b^HCW: health care worker.

^c^N/A: not applicable.

#### Quantitative Survey Participants

At baseline, before intervention implementation, community members were sampled through a random selection of households in all 60 study communities. In each community, 10 households were selected following a random walk procedure adjusted to the local context of widely spread farmsteads [45]. In each selected household, one female and one male household member were interviewed, preferably the household head and respective spouse or husband. For the endline survey, the same individuals will be interviewed. All CHVs will be selected for a quantitative survey during the endline data collection.

#### Qualitative Interview and Shared Walk Participants

We will conduct IDIs with 5-10 HCWs and CHVs in each of the intervention and control arms. In this phase, we will also invite selected 15-20 IDI respondents to participate in a “shared walk” to walk through their community and show research assistants (RAs) where their work takes place, what locational influences there are on their work, and how they feel anything influences their work in relation to leprosy. We will also conduct IDIs with community members in each of the intervention and control arms (30-45 members in total) to understand (depending on the intervention assignment) their perceptions of the services being offered, the sensitization campaign, and their feelings and experiences regarding leprosy.

A total of 3 RAs will conduct the IDIs and shared walks using standardized instruments. These include a participant information sheet, a consent form, a cover sheet, and interview guides (Table 1). Cover sheets will capture sociodemographic data, including sex, age, employment status, children, partner status, and religion. Cover sheets also include a section for RAs to make reflexive and observational notes. Written informed consent will be obtained from all study participants before beginning interviews. Depending on the preference of the participants, IDIs will be conducted one-on-one in a local language or French and will be audio-recorded. Participants in the IDIs will be asked broad, open-ended questions regarding topics such as the training, the intervention and audio tool, stigma, and perceptions of leprosy. IDIs will be designed to elicit personal responses and then lead to more in-depth and specific narrative-building questions. RAs will probe themes that seem to be of relevance to the participant or that are identified as important recurring themes through the debriefing process.

The “shared walk” will follow the tenets of the docent method defined by Chang [46] to provide more place-based data. The participants decide the route and duration of the walk. The RA will ask the participant to show them locations on the walk that are of significance to them for any reason, but will also ask the participant to show locations that are of particular relevance for the work they do and where significant events (such as education or outreach) take place. Each participant is considered to be an expert guide. The participant is the educator, while the RA is the person who needs to learn from and follow the lead of the participant. These walks will be audio recorded and can be supported by photos if the participant wishes to take them. Any photographs submitted in which it is possible to identify individuals will be anonymized.

### Data Analysis

#### Quantitative Analysis

Our primary analysis will be based on intention-to-treat at the individual level using linear regression comparing the outcomes of intervention and control arms. We will measure our primary outcomes in terms of absolute scores and as a percentage of the total possible score. We will use adjusted standard errors for clustering at the community level, our unit of randomization [47]. We will control for a number of baseline covariates, including gender, age, and education, among others.

#### Qualitative Analysis

Analysis will begin in the field with systematic debriefings. Debriefings are daily meetings with RAs and are designed to identify where interview questions are gaining in-depth responses and where questions need to be changed or refined [48]. Debriefings will also allow the research team to gain a superficial understanding of the main topics arising from the interviews and the shared walks, so that an initial codebook can be developed [48]. Once all data have been collected, IDIs will be translated, transcribed, and managed using NVivo (version pro 12; QSR International) [49]. We will follow a reflexive thematic analysis approach using the recursive 6 stages of analysis as defined by Braun and Clarke [50]. Data analysts will independently read and re-read transcripts for data familiarization. Transcripts will then be inductively analyzed in blocks of 5, and codes will be reviewed to identify similarities or divergence of ideas. This process will be followed until the coding is complete. The main codes will be presented to the study team to decide where reoccurring codes could build our core themes. After revising the codebook, we will develop a thematic scheme that will be presented to the study team, refined, named, and finalized for interpretation and writing.

Our mixed methods process will follow a sequential approach where we begin with quantitative data collection and analysis and, upon completion, start the qualitative component [51]. We assume that the quantitative data will allow us to develop more focused qualitative questions and that the qualitative data will help us to address any gaps in information that we cannot explain through the quantitative results. Further mixing of the 2 methods will occur during the data analysis of both data sets, when we will combine the qualitative and quantitative to present our findings to support the interpretation of the results. As such, we envision the shared walk data to allow us to identify potential intervention improvements with respect to the information provided, the dissemination of this information, and, in particular, participant understanding of the audio tool.

### Ethical Considerations

This study was approved by the Togolese Bioethics Committee for Health Research (025/2022) and the Ethics Commission of the Medical Faculty Heidelberg (S-670/2022), Germany. Before consent, information about the study will be provided (verbal or written). All participants will give (verbal or written) informed consent to participate in the research. Participants will not receive compensation for their participation. The data will be deidentified before analysis and securely stored in a password-protected file and on a password-protected computer. Any photographs submitted during qualitative data collection, in which it is possible to identify individuals, will be anonymized. The trial is registered at the German Clinical Trials Register (DRKS-ID: DRKS00029355).

## Results

Data collection started in March 2023 and is planned to be completed in June 2024, with ongoing data analysis. Analysis of the quantitative baseline data has been initiated, and results are planned to be submitted for peer-reviewed publication in the second quarter of 2024. The first quantitative endline and qualitative results are expected to be submitted for publication by the end of 2024.

## Discussion

We will use the mixed methods cRCT to measure the causal effect of community sensitization campaigns and audio tools distributed to households on knowledge and stigma related to leprosy. The setting of this study is rural communities in Togo, West Africa. Our nested qualitative components, involving interviews and shared walks with community members and local stakeholders such as CHVs and HCWs, will explore the implementation of the intervention and contextualize the quantitative results of the trial, while also helping to further characterize the mechanisms through which sensitization campaigns and audio tools affect leprosy-related knowledge and stigma.

The contribution of this study to the literature will be 3-fold. First, we will provide causal evidence on the effectiveness of sensitization campaigns on community-level leprosy-related knowledge and stigma. The literature on this is limited, especially in the West African context. Second, we will test novel audio tools for information dissemination to amplify potential campaign effects. The tools are designed to overcome literacy and language barriers in a multilingual context. Third, our results will contribute to the general understanding of leprosy-related stigma in the West African context. The qualitative and quantitative findings will inform policy makers and public health agents to effectively tailor and implement sensitization campaigns, particularly in challenging rural settings.

A potential limitation of this study is the fact that quantitative stigma indicators are self-reported by community members; this outcome might be affected by social-desirability bias. We will test intervention effects on the respondent’s knowledge of the disease, which is a key driver of stigma and not prone to social desirability bias. Further, qualitative IDIs with unaffected and affected community members will allow us to triangulate quantitative findings on stigma.

This cRCT serves to provide rigorous scientific evidence about the causal effectiveness of 2 particular interventions in the broader field of health-related stigma interventions and multilingual low-literacy settings. The results will be beneficial for policy makers and public health agents to guide sensitization campaigns and inform them about the potential of audio tools to complement common practice.

